### METHOD OF ASSESSMENT OR SCORING

The EEG is divided in 10-minutes epochs. The quality of all EEG epochs is visually assessed without knowledge of allocation group (experimental or control). Epochs showing artifacts that could affect the quantitative analysis are discarded.

IBIs are measured by using an automated algorithm and averaged in each 10-minute epoch. The IBI detector algorithm is based on a non-linear energy operator that reflects both amplitude and frequency content of the EEG. Power spectral analysis is performed using fast Fourier transformation with a time base of 10 seconds. For every epoch, total and relative (%) band power is calculated within the following frequency bands: delta (0.5–4 Hz), theta (4–8 Hz), alpha (8–13 Hz), and beta (13–30 Hz).

If more than one 10 minutes epoch is analysed, the simple average of all measures is used for further analysis

### Abbreviations

|             |                                           |
|-------------|-------------------------------------------|
| aEEG | Amplitude-integrated electroencephalogram |
| EEG  | Electroencephalogram                      |
| IBI  | Interburst interval                       |
| Hz   | Hertz                                     |

## 15.4 Appendix D: Procedures for MRI examination

### OUTCOME MEASURES

Outcome measure 1: Brain injury score according to Woodward with cerebellum score

Outcome measure 2: Volumetric measurements:

Outcome measure 3: Cortical folding with formation of the sulci:

Outcome measure 4: Diffusion tensor imaging:

### MEDIUM

Cerebral MRI scan

### TIME OF COLLECTION

At 40-44 weeks of gestational age.

### METHOD OF ASSESSMENT of brain injury scoring and quantitative measurements

The MRI protocol consists of anatomical scans preferable on 3Tesla MRI (T1 3D weighted image and T2 weighted image), DWI and DTI. The T1 and T2 weighted images are performed in coronal slices and the T1-3D weighted image at around 100-110 slices. The DTI images are performed in axial slices covering the whole brain. The focus is on the following features: brain tissue volumes, including myelinisation, cortical folding with formation of the sulci, in relation to DWI/DTI. All assessments are conducted without knowledge of allocation group (experimental or control).

### Brain injury score according to Woodward plus cerebellum:

The scoring system for the composite white matter and gray matter scores consists of eight assessments each using a 3-point scale.

**White matter abnormality** is graded using five areas of assessment within the white matter with a score of 1 (normal), 2 (mild abnormality) and 3 (moderate-severe abnormality) for each area of assessment. The five areas of white matter abnormality that are scored include:

**1. The nature and extent of white matter signal abnormality** - This is scored based on the T1- and T2-weighted signal abnormalities in the white matter best observed in the axial imaging.

Grade 1: normal T1- and T2-weighted signal throughout the white matter.

Grade 2: focal regions of high T1-or T2-weighted signal (2 or fewer regions per hemisphere).

Grade 3: multiple regions of high T1- or T2-weighted signal (more than 2 regions per hemisphere).

**2. Periventricular white matter volume loss** – This is also scored based on the combined T1- and T2-weighted imaging analyzing the ratio of periventricular white matter to ventricular volume in both the axial and sagittal imaging.

Grade 1: normal periventricular white matter volume usually associated with small ventricles

Grade 2: mild reduction in white matter volume with mild to moderate increased ventricular size.

Grade 3: marked reduction in white matter volume often occurring with marked increase in the size of the ventricle and/or extra-axial space.

**3. Cystic abnormalities** – This is easily assessed on any imaging view or modality but occurs rarely.

Grade 1: normal, with no cystic abnormality.

Grade 2: less than 2mm single focal cyst.

Grade 3: multiple cysts or a single larger (2mm or greater) single focal cyst is rare.

**4. Ventricular dilatation** – This is also scored based on the combined T1- and T2-weighted imaging in both the axial and sagittal imaging.

Grade 1: normal with no evidence of ventricular dilatation.

Grade 2: moderate enlargement resulting in mild rounding of the frontal horns, minimal enlargement of the temporal horns and moderate enlargement of the occipital horns.

Grade 3: more global enlargement of a moderate to severe nature including significant enlargement of the frontal, temporal and occipital horns.

**5. *Thinning of the corpus callosum*** – This is scored based on the sagittal and coronal T1-weighted MR imaging.

Grade 1: normal, with thick corpus callosum visible in all views.

Grade 2 :focal thinning in the corpus callosum often visible in the mid region of the body of the corpus on sagittal images.

Grade 3 :global thinning across the entire corpus callosum.

5 assessments of the cerebral white matter are then combined to give an overall white abnormality score which is categorized as:

- no abnormality - Total score 5 to 6
- mild abnormality – Total score 7 to 9
- moderate abnormality – Total score 10 to 12
- severe abnormality – Total score 13 to 15.

**Gray matter abnormality** is graded using three scales assessing:

**1) *Presence of gray matter cortical signal abnormality*** . This is very rarely detected and thus does not contribute significantly to the overall scoring. It is scored on high signal intensity in the cortex on axial T1 and/or loss of cortical ribbon signal on axial T2-weighted MR imaging.

**2) *Quality of gyral maturation*** – Cortical gyration maturation is rated by standard gyral model (3,4) using representative MRI images and cerebral models of gyral development at 34 weeks, 36 weeks, 38 weeks and 40-42 weeks on axial T1- and T2-weighted MR imaging. The gyral pattern assessment in these maturational assignments includes at 34-36 weeks the presence of marginal sulcus, paracentral gyrus with secondary sulci present in the frontal lobes, superior and middle temporal, rolandic and occipital regions. By 36-38 weeks the gyral pattern should include additional secondary gyri in the transverse and inferior temporal and cingulate gyri. At 40 weeks' gestation there would be tertiary inferior temporal and inferior occipital gyri and sulci. Grade 1: normal for 40 weeks.

Grade 2: 2 to 4 weeks delay in gyral development (i.e. consistent with 36 to 40 weeks).

Grade 3: more than 4 weeks delay in gyral development.

**3) *Size of the subarachnoid space*** - This is scored based on the sagittal T1 and coronal T1- or T2-weighted MR images for the size of the subarachnoid space in relation to the cerebral mantle.

Grade 1: small subarachnoid space which is barely visible.

Grade 2:mildly enlarged CSF space with visible enlargement of the space between the major sulci and the interhemispheric space in addition to the extracerebral space.

Grade 3: more substantially enlarged global subarachnoid space with visible cerebrospinal fluid between many gyri as well as interhemispheric and extracerebral.

The total gray matter score was then calculated and categorized as

(a) normal - score 3 to 5

(b) abnormal score 6 to 9.

#### **Cerebellar lesions:**

(a) normal: no lesions

(b) mild: < 6 punctate lesions

(c) moderate /severe: > 6 punctate lesions/cerebellar hemorrhage

**Volumetric measurements:** The segmentation is performed on the MR images of individual participants. The segmented tissue types include: unmyelinated and myelinated white matter, cortical and central gray matter (basal ganglia and thalamus), cerebro-spinal fluid around the brain, ventricles, cerebellum and brainstem. This segmentation method was developed for neonates (87). Quantitative measurements of the cerebral tissue volumes are performed by the knn-approach segmentation method which is based on the probability of each tissue classes from signal intensities in T1- and T2-weighted images and the anatomic location. Thereafter, the volume of each tissue is quantified.

**Cortical folding with formation of the sulci:** For cortical folding, the inner cortical surface is segmented and reconstructed in 3D from the T2-weighted images. The surface is detected between the developing cortex and white matter zone. The global area of this inner cortical surface is then computed. The segmentation of the inner surface is used as it highlights the cortical sulcation pattern more precisely than the outer surface, particularly where sulci are still not deeply folded. Finally, the local surface curvature is estimated from the mesh local geometry: positive curvatures correspond to the gyri top, and negative curvatures to the folds bottom. So the 3D image is then created. The sulci are defined as connected components of negative curvature and labelled manually according to post-mortem and MRI atlases and prenatal images. To characterize the sulci maturation according to gestational age, their sulci areas will be calculated. Thereafter, for each infant, the sulcation index with total cortical surface and thickness can be computed. Sulcation index is defined as the ratio between the areas of sulci and the surface of the total cortex. This surface increases with the age-related brain growth. The sulcation index, thus, characterizes the proportion of sulci according to the whole brain size, and is a measure of maturation of the cortex.

**Diffusion tensor imaging:** (DTI) scans are obtained to perform analyses of the diffusion coefficients on the brain averages, as well as on individual participants. It visualizes the movement of fluid in the brain, and can be used to identify white matter tracts. We will study the maturation of white matter fiber tracks in relation to cortical development.

#### Abbreviations

|            |                            |
|------------|----------------------------|
| DWI | Diffusion weighted imaging |
| DTI | Diffusion tensor imaging   |
| MRI | Magnetic resonance imaging |
| T1  | T1-weighted                |
| T2  | T2-weighted                |
| 3D  | Three-dimensional          |

## 15.5 Appendix E: Procedure for assessment of cranial ultrasound

### OUTCOME MEASURES

Outcome measure 1: Parenchymal/periventricular haemorrhagic infarction / inhomogeneous flaring

Outcome measure 2: IVH Grade III

Outcome measure 3: Cerebellar haemorrhage

Outcome measure 4: Posthaemorrhagic hydrocephalus

Outcome measure 5: cPVL

Outcome measure 6: Cerebral atrophy

### MEDIUM

Sonogram

Coronal:

C1 frontal lobes

C2 foramen Monro

C3 lateral ventricles with largest size of VI

C4 cerebellum largest diameter left-right

C5 posterior horns with plexus

C6 periventricular

Sagittal

S1 midline

S2 left lateral ventricle

S3 left periventricular through fissura Sylvi

S4 right lateral ventricle

S5 right periventricular through fissura Sylvi

Cerebellum via mastoid with transducer in coronal position such as coronal view via anterior fontanel

### TIME OF COLLECTION

- Early scans (day 1,4):
- Late scans (day 7, 14, 35)
- Term scan: 40-44 weeks of gestational age

### METHOD OF ASSESSMENT OR SCORING

The assessment classification is:

1. Normal brain scan

- No cysts
- No ventricular dilatation
- No enlargement of extra-cerebral spaces
- Normal cortical grey matter

2. Mild brain injury:

- Grade 1-2 IVH (including GLH)
- Persistent pathologic non-decreasing inhomogeneous flaring at day 7 and 14
- Thinning of the corpus callosum
- Ventriculomegaly at term, ventricular index < p97

3. Severe brain injury will be defined as

- Intraventricular haemorrhage grade III (ventricular index > p97 during the acute phase)
- Posthaemorrhagic ventricular dilatation

- Parenchymal/periventricular haemorrhagic infarction
- Local cystic lesions (unilateral)
- Cystic periventricular leukomalacia (bilateral)]
- Cerebellar haemorrhage
- Cerebral atrophy at term age (ventricular dilation and/or increased extra-cerebral spaces

All assessments are conducted without knowledge of allocation group (experimental or control).

#### **Abbreviations**

|             |                                     |
|-------------|-------------------------------------|
| IVH  | Intraventricular haemorrhage        |
| cPVL | Cystic periventricular leucomalacia |
| cUS  | Cranial ultrasound                  |

## 15.10 Appendix J: SafeBoosC - Data flow

### SafeBoosC - Data flow

#### Web-based Case Report Form

The CRF will be a web-based solution in the open source clinical trials software OpenClinica®. This will handle the inclusion procedure, the documentation of the stratification and randomisation process, the adverse reaction and the relevant clinical data from the patient apart from rStO2 and interventions plus physiological parameters. The data will be entered into the CRF by keying by the medical staff. A form for the inclusion, the randomisation, the NIRS monitoring period, the term follow up, and the two-year follow up will be created. Serious adverse reactions will be reported directly to the sponsor within 24 hours.

#### Regional tissue oxygen saturation rStO2

Each oximeter will be connected to a laptop computer through serial port that will display or blind the values of rStO2. A dedicated software solution designed to SafeBoosC data acquisition will handle the NIRS data. The 0.2 Hz rStO2 numeric values will be stored continuously in CSV file with a data and time code on the laptop throughout the monitoring period of 72 hours. If the oximeter provides information on signal quality this will be recorded simultaneously. The CSV file will be labelled with the patient trial identification number (trial-ID). At the end of the monitoring period the CSV file of 5-10 MB will be uploaded to Copenhagen Trial Unit (CTU) that will store the data and perform the data analysis. If the file is not uploaded within 2 workdays the relevant investigator will be contacted.

#### Treatment guideline interventions

If interventions from the treatment guideline are initiated due to an out-of-range rStO2 the type of intervention, the current values of rStO2, SpO2, MABP, and pCO2 will be entered by the

attending medical staff by simple keying into a software solution designed to SafeBoosC data acquisition. Depending on the intervention the data acquisition software will prompt the staff to enter the values again 30 and 60 minutes or 60 and 240 minutes afterwards. Each possible intervention will be given specific number. The interventions and values will be recorded and stored in the same CSV file as the rStO2 values and uploaded to Copenhagen Trial Unit at the end of monitoring period.

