**Figure 2: SafeBoosC Trial timeline**

### 3.4 Blinding

Due to the nature of the intervention, the intervention cannot be blinded for the clinical staff and the parents. However, blinding will be used in all other aspects of the trial. Firstly, the allocation sequence will be concealed for the investigators and all other trial personnel. Secondly, some

outcomes, including the primary, will be assessed by an outcome assessment committee (centrally), blinded to the allocation of the participants. Thirdly, the statistical data analyses will be performed with the two intervention groups concealed as, e.g., X and Y. Finally, two conclusions of the results of the trial will be drawn – one presuming X is the experimental group and Y the control, and one assuming the opposite. Hereafter, the blinding will be broken.

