**Table 1: Assessment tools and outcome measures**

| Tools                  | Outcomes                                                                                                                                                                                       | Time points*                                                                                         | Centralised reading #                   |
|------------------------|------------------------------------------------------------------------------------------------------------------------------------------------------------------------------------------------|------------------------------------------------------------------------------------------------------|----------------------------------------------------|
| Cerebral NIRS oximeter | 
 
Burden of hypoxia
 
Burden of hyperoxia
 
                                                                                               | 
 
During the intervention until 72 hours after birth
 
 | Department of Neonatology, Rigshospitalet, Denmark |
| aEEG/EEG (Appendix C)  | 
 
Interburst interval (IBI)
 
Power in delta band
 
Power in theta band
 
Power in alpha band
 
Power in beta band
 
 | 
 
64 hours after birth
 
                               | Uppsala University, Sweden                         |

| Tools                                                                                                                                                                                                                                                                 | Outcomes                                                                                                                                                                                                                           | Time points*                                                                                                                                                                                                                                                                                                                 | Centralised reading #                                                              |

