| Investigator's
assessment and
medical records                                                                                                                                                                                                                   | Therapies implemented: 
 
• Mechanical ventilation
 
• Volume substitution
 
• Blood transfusion
 
• Inotrope
 
• Vasopressor
 
• Ductal closure
 
 | 
 
• During the intervention until 72 hours after birth
 
                                                                                                                                                                                                                       | Not centralised                                                                               |
| CRF                                                                                                                                                                                                                                                                   | Physiological parameters 
 
• Mean BP
 
• Mean SpO2
 
• Mean pCO2
 
                                                                                                     | 
 
• During the intervention until 72 hours after birth
 
                                                                                                                                                                                                                       | Not centralised                                                                               |

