### **Electroencephalogram**

Single-channel EEG is applied for at least 120 minutes at 56-72 hours after birth. Electrodes are placed at positions P3 and P4 according to the international 10–20 system; a frontal reference electrode is also applied. The raw data file (5-10 MB) is labelled with the trial-ID and up-loaded to the CTU. The ID of the files will be recoded before transfer to Dept. Of Neonatology, Rigshospitalet, Copenhagen, Denmark for centralised final analysis.

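### Appendix J stores the guideline-intervention log in the primary-outcome file with no separation step, and it contradicts Table 1 on where physiology is recorded

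*Protocol*

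**What the plan says.** **Blinding.** Section 3.4 concedes that clinical staff and parents cannot be blinded, but says that some "outcomes, including the primary, will be assessed by an outcome assessment committee (centrally), blinded to the allocation of the participants". Table 1 names a central reader for the NIRS oximeter, the neonatology department at Rigshospitalet, and its footnote says central assessment is by a blinded committee.

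**The NIRS file.** Appendix J (Regional tissue oxygen saturation) has a laptop store the rStO2 values at 0.2 Hz in a CSV file, with signal quality where the device supplies it. The file carries the trial-ID and goes to the Copenhagen Trial Unit for storage and analysis.

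**The intervention log.** The next part of Appendix J begins "If interventions from the treatment guideline are initiated due to an out-of-range" rStO2. Staff then key in the type of intervention with the current rStO2, SpO2, MABP and pCO2, and are prompted for the values again later. On storage it says: "The interventions and values will be recorded and stored in the same CSV file as the" rStO2 values.

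**The CRF.** Appendix J (Web-based Case Report Form) says the CRF handles the relevant clinical data apart from rStO2 "and interventions plus physiological parameters". Section 7.1.2 makes the eCRF the primary entry point for all trial data not taken from the NIRS device. Table 1 gives the CRF as the tool for "Physiological parameters" (mean BP, SpO2 and pCO2 up to 72 hours), and the investigator's assessment and medical records as the tool for therapies.

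**EEG.** Table 1 places the central reading at "Uppsala University, Sweden". Appendix J says the file IDs are "recoded before transfer to Dept. Of Neonatology, Rigshospitalet, Copenhagen, Denmark for centralised final analysis".

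**The concern.** The file from which the primary outcome is derived also holds a record that only one arm can generate. Someone who opens it to check signal quality or reject artefact may see the allocation while deciding which data count. The trial cannot blind bedside staff, so blinded central assessment is one of its main remaining protections for the primary outcome.

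The second issue is the source of therapy and physiology data. These are exploratory outcomes in Section 6.3, and they are what would help to explain a change in burden. If one arm is recorded at abnormal moments and the other on a different basis or not at all, the arms cannot be compared fairly. These matters are not left to a later analysis plan: the protocol itself fixes the data flow, the reading centres and the blinding.

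**Working it through.** The protocol gives no figure to reproduce here. The check sets its statements side by side.

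**1. Can a log entry arise in a control infant?** The trigger is a guideline intervention started for an out-of-range rStO2 (Appendix J). In the control group the reading is hidden behind a locked box and care is as usual (Sections 3.2 and 5.3); staff see only the signal-quality indicator. Under the protocol, no such entry can arise. So a file with an entry comes from an experimental infant, while a file without one may come from either arm.

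**2. Is the log removed, or the file recoded, before reading?**

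| Data | Step stated in Appendix J before central reading |
|---|---|
| Cerebral ultrasound | ID recoded before transfer |
| EEG | ID recoded before transfer |
| MRI | ID recoded before shipment |
| NIRS (primary outcome) | Trial-ID label only; no recoding or separation stated |

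The safeguard is written for three readings and not for the primary outcome. It is also unclear who reads the file: Table 1 names the Rigshospitalet department, whereas Appendix J has the trial unit perform the analysis. The sample-label example in Appendix B shows that Rigshospitalet enrols participants, so an unrecoded trial-ID could be recognised there.

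**3. How much room is there for judgement on the data?** The burden is a numeric sum of deviations over time, corrected in the pilot for lost recording time (Section 10.1). Pilot recordings were reliable 79% of the time, with a range of 48% to 97%. Assuming that these percentages refer to the full 72 hours:
- Typical time lost: (1 − 0.79) × 72 = 15.1 hours.
- Range of time lost: (1 − 0.97) × 72 = 2.2 hours to (1 − 0.48) × 72 = 37.4 hours.
- If the correction is proportional, the scaling factor is 1/0.79 = 1.27, ranging from 1/0.97 = 1.03 to 1/0.48 = 2.08.

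Rules for accepting data therefore matter to the endpoint. These figures show how much data is subject to acceptance or rejection. They do not measure bias: the pilot used one device series and its censoring was done by software.

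**4. Where are therapies and physiology recorded?**

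| Place | Physiology | Therapies |
|---|---|---|
| Table 1 | CRF, to 72 hours, no restriction by arm | Investigator's assessment and medical records, no restriction by arm |
| Section 7.1.2 | eCRF | eCRF |
| Appendix J, CRF part | Excluded from the CRF | Interventions excluded from the CRF |
| Appendix J, interventions part | Keyed with a guideline intervention | Guideline interventions only |

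The first two rows describe collection in both arms, and the last two do not agree with them. If only Appendix J were followed, physiology would exist for experimental infants at out-of-range moments and at the prompted follow-up times. That is a sample selected on the outcome and on the arm, and it is not a 72-hour mean.

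**5. EEG.** The two reading centres differ. Interburst interval is a secondary outcome, and Appendix C has epochs accepted or discarded by eye.

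**The case against.** A reader might infer that the primary-outcome reader is in fact unblinded. The protocol does not support that. Nowhere does it say that the central reader receives the intervention entries; the file goes to the trial unit, and Section 7.1.1 refers to specialised software. The trial protocol describes no manual artefact step, and Section 3.4 has the statistical analysis done with the groups masked. These points stand and reduce the finding to a possible route. They do not close that route, because no separation is stated and recoding is stated for the other three central readings.

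A reader might also infer from the pilot mean burden of 76.0 %hours that nearly every experimental infant would be identifiable. That does not follow. The burden measures exposure, not logged actions; its distribution is right-skewed (SD 83.2), and Appendix A asks staff only to consider an intervention, and only when spontaneous normalisation is not expected.

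A third tempting reading is that control infants have no physiology or therapy data, 0 of 83. Table 1 and Section 7.1.2 name sources that apply to both arms. Appendix J itself plans a CRF form for the monitoring period ("A form for the inclusion, the randomisation, the NIRS monitoring period, the term follow up, and the two-year follow up will be created"), and Table 2 schedules infant concomitant medication during the intervention. The excluding clause may have been meant only for the event log. That is plausible, but the clause carries no such limit, so the contradiction remains.

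Finally, it can be said that EEG blinding is protected wherever the reading is done, because the IDs are recoded. That is right. Requiring a centre that did not treat the infants would be a preference, and only the conflicting names need correcting.

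**Conclusion.** The point holds in a limited form.

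- **Blinding of the primary outcome.** The stated data flow leaves a route by which allocation could be seen, contrary to Section 3.4 and Table 1. It applies to experimental files with at least one logged intervention, and it matters only where someone decides whether to accept or reject data. The protocol gives neither the number of such files nor the effect of such decisions, so no bias can be quantified. The conclusion assumes that the file is read as stored and that control entries do not occur.
- **Therapies and physiology.** The defect is an internal contradiction, not a demonstrated absence of control data. The harm arises only if Appendix J is followed literally, and it affects exploratory outcomes.
- **EEG reading centre.** This is a clerical inconsistency.

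The first two should be corrected, because the remedies are specific and nearly free. Neither calls the sample size or the primary analysis model into question.

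**What to change.** 1. In Appendix J, state that the trial unit extracts rStO2, time stamp and signal quality under a recoded ID for the blinded primary reading, and withholds the intervention log until that reading is locked. State who performs the reading, so that Table 1 and Appendix J agree.
2. Correct the CRF and intervention parts of Appendix J to match Section 7.1.2 and Table 1: therapies and mean BP, SpO2 and pCO2 are recorded in the same way in both arms, and the event log is described as a supplement.
3. Name one EEG reading centre in both Table 1 and Appendix J, and keep the recoding.

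The cost is a file-splitting script, a text correction and some data entry that Table 1 already implies. No clinical rule changes.
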